## Abstract

**Introduction:**

Individuals experiencing moderate to severe mental illness have low rates of workforce inclusion, with a consequence of high welfare dependency, affecting both societal costs and health. Individual Placement and Support (IPS) is an approach to supported employment where the goal is to help people obtain jobs on the open rather than sheltered labour markets. Despite multiple randomised controlled trials (RCTs) indicating that the IPS model enables employment better than treatment as usual, with widespread adoption in some jurisdictions, the broader impacts of this large-scale implementation on mental health, quality of life and social functioning remain unknown.

**Ethics and dissemination:**

This is an effectiveness study using registry data. The Regional Committee for Medical Research Ethics Northern Norway, REK North has approved the use of registry data without informed consent for this project (approval number 134553).

The findings will be disseminated both in academic peer-reviewed journals, directly to informants in WP1, to the public through media and the project website, and at relevant conferences and seminars for specific relevant target groups.

**Trial registration number:**

Not applicable

STRENGTHS AND LIMITATIONS OF THIS STUDYThis study leverages a national staggered rollout of Individual Placement and Support (IPS) in Norway, allowing for a robust difference-in-differences design to assess population-level effectiveness beyond controlled experimental conditions.By using high-quality, nationwide administrative registries covering health, employment, welfare, crime and mortality, the study ensures minimal attrition and enhances the validity and reliability of outcomes.Relying on local site reports to capture IPS implementation intensity introduces a risk of recall or reporting bias.We have limited knowledge of interventions and initiatives in the control group. To the extent there are IPS-like activities in the control group, this would introduce bias in favour of the nil hypothesis.As an observational (non-randomised) design, residual confounding may persist despite efforts to adjust for baseline differences.

## Introduction

 Work is central to well-being, providing income, identity, structure and social connection.^1 2^ Employment is linked to lower rates of loneliness^3^ and suicide,^4^ and extensive evidence shows better physical and mental health among employed people across time, settings and socioeconomic groups.^15^,^7^ Despite advances in treatment, most people with severe mental illness (SMI) remain excluded from the workforce.^1^,^5^ Employment typically declines with continued service contact,^8^ though many regard employment as central to recovery and an important treatment goal.^9^,^13^

Work has long been regarded as integral to mental health treatment, contributing to purpose, self-efficacy and belonging.^14^,^16^ During the 20th century, work moved from being viewed as a form of therapy to being considered a human right. Over the last 40 years, vocational rehabilitation has evolved into two main models: traditional vocational rehabilitation (‘train and place’) and supported employment (‘place and train’), such as Individual Placement and Support (IPS). Developed in the 1990s in the USA, IPS helps people with serious mental illness gain employment through a rapid ‘place-then-support’ approach,^17^ and the model is internationally recognised as the most effective evidence-based practice for helping people living with SMI obtain competitive employment,^18 19^ with demonstrated superiority over all other forms of vocational rehabilitation. It is based on eight evidence-based principles, is manualised^20^ and has a fidelity scale^21^ to assess whether it is being implemented as intended. Meta-analyses of IPS randomised controlled trials (RCTs) consistently find employment rates to be more than double compared with other vocational rehabilitation approaches regardless of diagnostic, clinical, functional and personal characteristics.^22 23^ Furthermore, systematic reviews of its cost-effectiveness find a strong economic case for implementation.^24^

Increasingly, IPS is being recommended within national mental health treatment guidelines for people who wish to gain and retain employment.^25^,^27^ Policy makers see strengths of IPS being the strict fidelity adherence and the continuous monitoring of the implementation rules.^28^ Internationally, IPS is available in over 20 countries,^29^ many of which are undertaking expansions supported through national strategies and targeted funding.^30^,^32^

Mental health conditions remain the leading contributor to years lived with disability (YLDs) for young people aged 10–24 and the second highest contributor to YLDs for all age groups in high-income countries.^33^ The increase in disability rates among young people is particularly concerning, and the increase among young people is predominantly for mental health conditions.^34^ In Norway, mental health conditions are now the main reason for claiming disability pension—surpassing musculoskeletal disorders in 2011.^35^ During the same period, the prevalence of disability among young people due to mental health conditions has increased by almost 50%,^34^ while disability among older people has remained largely stable. This raises significant social, political and economic concerns, as they contribute to a widening employment gap.

RCTs have demonstrated IPS effectiveness at the individual level in countries with different labour markets, welfare systems and economic conditions, with little effect on outcomes.^22 36^ A recent Norwegian study found a significant, positive, causal effect on societal-level employment outcomes for young adults in a municipality where IPS was implemented compared with municipalities where it was not.^37^ In the Netherlands, a national evaluation of IPS^38^ found similar results comparing outcomes for disability benefit recipients with mental health conditions receiving IPS to a control group receiving traditional vocational rehabilitation services.^39^ While this emerging evidence for a societal impact is encouraging, whether the IPS expansions can produce population-level health and economic benefits (and implications for societal well-being) remains unknown.

Crime is another relevant societal outcome, given its substantial social costs.^40^ People living with mental health conditions are more likely to be victims of crime and have higher rates of contact with the criminal justice system, partly due to poverty, social exclusion and increased risk of drug and alcohol dependency.^41 42^ Whether supported employment programmes such as IPS influence crime at the societal level remains unknown, and will be explored in the current study. The IPS method is costly, and the implementation of IPS services implies increasing the initial outlay to society in expenses for people with mental health conditions. Our previous systematic review^24^ indicates that IPS can be cost-effective from a health system perspective, but these data mainly cover short time periods of under 2 years.

The IPS implementation in the Rest of Norway (IPSRON) study aims to address these knowledge gaps in an effectiveness trial where we will ascertain the societal footprint of IPS implementation at a national level in Norway.

## Methods and analyses

### Study design and setting

The IPSRON project is an effectiveness study using registry data to study the effect of IPS implementation in Norway between 2012 and 2019, as the pandemic hampered further rollout of IPS from 2020.^43^ The project commenced in 2019 and will continue to 2027. It will examine the effect of implementing IPS on society at large, thus studying the effectiveness (as opposed to the efficacy) of IPS. This is the same approach as our study examining the effectiveness of implementing IPS in one Norwegian municipality compared with some control municipalities.^37^ The research project is led by the Centre for Work and Mental Health, Nordland Hospital Trust, Bodø, Norway.

Naturalistic trials, or *natural experiments*, generally involve no active intervention by the researcher. Instead, they rely on observations of phenomena occurring within real-world contexts. Unlike RCTs, natural experiments are not bound by the same temporal, practical or ethical constraints. This allows for analyses over longer timeframes, the inclusion of additional outcome measures and the use of larger (in some cases whole-population) datasets. These features can produce markedly different findings on efficacy and effectiveness. For example, studies comparing long-acting injectable antipsychotics (LAIs) with oral antipsychotics have shown that observational studies often report greater benefits of LAIs than do RCTs.^44^ In Norway, variation in service provision (despite national guidelines and a unified public health and welfare system) combined with substantial geographical diversity creates a unique natural laboratory for research. When coupled with Norway’s world-class health and social registries, this variation enables robust causal analyses of real-world treatment effects on long-term outcomes, generating evidence that can directly inform practice and policy.^45 46^ In the present study, we exploit regional differences in the timing of IPS implementation as a natural experiment to evaluate its effectiveness at the population level.

### Setting

Norway is a high-income nation with low unemployment rates, high job security and more evenly distributed income and wealth than most OECD (Organisation for Economic Co-operation and Development) countries,^47^ indicated by a Gini coefficient of 0.27 (perfect equality would have a value of 0 while 100 would be perfectly unequal).^48^ A key feature of the Norwegian welfare system is social security for the population. This includes free access to higher education, a social safety net for people with reduced health and income, and a universal publicly financed healthcare system.

The two decades following the publication of the World Health Report 2001, which focused on mental health, have seen many high-income countries implement different mental health system reforms. In Norway, reforms between 1998 and 2008^49^ aimed to increase autonomy, reduce dependency and therefore empower people living with mental health conditions. The balance between inpatient and community-based services was changed, with the number of hospital beds dramatically reduced. People were able to receive care and support from more rural psychiatric units rather than centralised large hospitals.^50^ However, this reform was unsuccessful in terms of promoting employment. The continued high number of young people in Norway receiving disability benefits signifies that, almost a decade later, we still have not translated increased access and support from local psychiatric units to greater employment.

### Mental healthcare

In Norway, the state is responsible for hospital and specialist healthcare services, while the municipalities are responsible for primary care and public health which include access to general practitioners.^35^ Specialist mental healthcare is organised through four regional health authorities that organise hospital care and district psychiatric centres. Approximately 250 000 people receive services from specialised mental healthcare annually. Most people are treated in outpatient clinics, assertive community treatment (ACT) teams or flexible ACT teams.^51^ In 2019, mental disorders and substance use disorders accounted for 20.7% of total health spending. For those aged 15–49, mental disorders and substance use disorders accounted for 46.0% of total health spending.^52^

### Work and welfare

The government-funded public employment service (Norwegian Welfare and Labour Administration (NAV)) provides all employment and welfare services in Norway and is thus a ‘one-stop shop’ in line with the international trend of transforming welfare systems.^53^ NAV’s main objectives include having more people employed and thus requiring fewer welfare benefits, the simplification and tailoring of services to meet individual needs and providing comprehensive and efficient labour and welfare support. Studies indicate that between 4 and 13% of people experiencing schizophrenia are working in Norway.^54^,^56^

### Individual Placement and Support in Norway

Since 1997, Norwegian health policy has prioritised the employment of people with mental health conditions,^49^ and in 2007, the Ministry of Labour and Social Inclusion and the Ministry of Health and Care Services jointly published a national strategic plan for work and mental health.^32^ This policy framework highlighted IPS and recognised the need for coordinated support and collaboration from health and social services and NAV to support individuals with mental health conditions to be able to work. In Norway, IPS therefore evolved from a mental health service model to one coordinated through NAV, supported by national resource centres, fidelity measures and national professional guidelines. Currently, around 100 services are operating and a nationwide rollout for young adults was launched in 2021.^57^,^59^ In 2012, a Norwegian IPS RCT for people with mental health conditions was commissioned which found IPS to be more effective than high-quality usual care for both vocational and non-vocational outcomes.^60^ Resources for the implementation of IPS were initially provided through earmarked funding from the Norwegian Directorate of Health (2012–2016) to six to eight pilot sites, covering staff positions, training and operational costs. Since then, resources have gradually expanded and changed. From 2017, funding and responsibility were transferred to NAV, supported by the Health Directorate and the Norwegian Resource Centre for Community Mental Health. National and regional resource centres, IPS advisors, training programmes, fidelity reviews and implementation toolkits were established to ensure quality and sustainability. These developments and resource changes are described in more detail in Moe *et al*,^57^ Moe *et al*,^61^ and Sveinsdottir *et al*.^62^ Some indications of programme drift have been reported: participants have expressed concern that IPS in Norway may deviate from the original evidence-based practice (Moe *et al*^57^) and similar patterns have been observed in other Nordic countries.^63^ A recent Norwegian status review of IPS, commissioned by the Directorate of Health, indicates that weakened integration between NAV and health services threatens a core element of IPS—integrated vocational and psychiatric rehabilitation—critical for individuals with severe and complex mental health conditions.^64^ While cultural and contextual adaptations of IPS are often necessary, research emphasises that such modifications should not compromise its core principles,^65^ which may be relevant in the Norwegian context.

### Work packages, data sources and methods

The three work packages (WPs) in the IPSRON project are inter-related but have distinct data sources and methods and are therefore presented separately. A schematic overview of the timeline for the WPs is presented in figure 1. A premise for the study is WP1, which was initiated in 2021 and completed in 2025. As it pertains to the work in WP2 and WP3, a description of WP1 is included in the section below, with further details described in a previous publication from this project.^58^ The data collected as part of WP1 will become available for linkage with the other data sources in the project in late 2025. Application for registry data to support analysis in WP2 was initiated in 2021–2022. In 2023–2024, the different data were received by the project from its respective registries, and data cleaning and linkage were initiated. In 2025, these data will be linked to the data provided by WP1, at which point all the necessary factors are in place to conduct analyses of the main outcomes of WP2. The economic evaluations of IPS will be informed by results from WP2.

**Figure 1 F1:**
[figure not shown]
Schematic overview of the timeline for the IPSRON project and work packages. IPS, Individual Placement and Support; IPSRON, IPS implementation in the Rest of Norway; WP, work package.

As we make use of complete population data rather than survey samples, this minimises the need for sample selection adjustments through matching procedures. Instead, we will carefully examine whether the identifying assumptions for difference-in-differences are plausible in our context. Specifically, we will:

Test the parallel trends assumption by comparing pre-intervention trends in outcomes across treatment and comparison areas.Assess the comparability of treatment and comparison groups with respect to demographic and socioeconomic characteristics prior to implementation.Use a staggered difference-in-differences design (DID), which has been shown to handle variation in treatment timing more effectively, and which we have previously applied with success in related work.^66^

Because Norwegian administrative registries capture nearly all specialist mental health service use and welfare data at the individual level, the study is not susceptible to significant dropout rates or missing data commonly seen in prospective studies. If substantial deviations from parallel trends are observed, we will conduct sensitivity analyses to explore the robustness of our findings, for example, by restricting to more comparable subgroups or using alternative model specifications.

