Using longitudinal registry data and a DID,^67^ we will explore the relative differences in outcomes between where IPS is available and where it is not. Since the rollout of IPS occurred at different times and intensities across Norway, a staggered DID estimation framework will be applied. Staggered treatment occurs when interventions vary in timing across units. The difference in timing will be analysed by year of IPS implementation, as such some participants will be in the control group the whole observation period, whereas others are controls until IPS exposure and in the intervention group after. This approach provides several advantages compared with conventional DID estimation, where the main one is the ability to use both units that have yet to implement IPS and those who never implemented IPS as controls for the analysis. Both the intervention group and the control group will be identified in the Norwegian Patient Registry. The intervention group is defined by residence in an area where IPS has been delivered, which is at about 70 teams in Norway at the end of the observation window 2009–2019. By 2019, IPS was present in all municipalities in Norway. In terms of access to the service, 70.9% of the population lived in an area where IPS was available.^58^

Leaning on data from WP1, we describe how we know when the target population group is potentially exposed to IPS at the psychiatric treatment units. In short, the target group will be defined (per year) by being between 18 and 45 years at inclusion and receiving treatment in public sector specialist mental health services. The cut-off at 45 years old reflects Norwegian policy at the time, as younger employees were initially given priority access to IPS; however, if participants exceed 45 years of age at follow-up, they will be included in the analysis.

The control group is defined as living in a municipality where IPS was not available, and beyond this, by the same criteria as the intervention group. Other forms of employment support will occur in the control group, and we do not have detailed knowledge of the interventions; however, treatment as usual is the common control condition for studies investigating IPS.^22^

As sensitivity analyses, we may also further restrict the sample to a subset with relatively lower income and/or welfare dependency at the time of first contact and not being in full-time education at the time of treatment.

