## Strengths and limitations

Unfortunately, it is a common problem in psychiatry that when implementing clinical procedures with evidence from RCTs, societal effects appear absent. There is sufficient evidence from RCTs for IPS efficacy. This project aims to investigate if effectiveness measured at the level of the society follows IPS implementation. Findings from this project will be key to ascertaining the actual output, or benefit on a societal level, of implementing IPS at scale. The strengths of this study include its design (effectiveness study), which permits investigating the societal footprint of IPS using a large longitudinal cohort. We use registry data without attrition and with high reliability and validity. The exposure to IPS is established by comprehensive interviews and complementary sources. A limitation of the study is related to potential self-report bias in WP1, causing some reliability problems in estimating intensity of IPS in the community. We have limited knowledge of similar interventions and initiatives in the control group. This would introduce bias in favour of the nil hypothesis. We also acknowledge that contextual factors, associated with the IPS intervention areas or not, could bias the analysis. We have limited the observation period to before the COVID-19 pandemic as this is known to influence IPS services.^43^ The many IPS catchment areas and control areas help reduce the risk of contextual factors introducing unobserved confounding. To ascertain IPS programme sustainability, a follow-up with data for 7–10 years beyond this study is needed.

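### Robustness analyses for differential trends run only if an undefined substantial deviation from parallel trends is observed; they should be reported whatever the pre-trend check shows

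*Protocol article*

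**What the plan says.** The relevant text follows Figure 1 in the section on work packages, data sources and methods of the protocol article. It opens with the reason for not matching, "As we make use of complete population data rather than survey samples, this minimises the need for sample selection adjustments through matching procedures", and continues: "Instead, we will carefully examine whether the identifying assumptions for difference-in-differences are plausible in our context". Three steps follow.

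- "Test the parallel trends assumption by comparing pre-intervention trends in outcomes across treatment and comparison areas".
- "Assess the comparability of treatment and comparison groups with respect to demographic and socioeconomic characteristics prior to implementation". No action is attached to an imbalance.
- Use of a staggered DID design.

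The section then gives the rule at issue: "If substantial deviations from parallel trends are observed, we will conduct sensitivity analyses to explore the robustness of our findings". Its examples are restriction to more comparable subgroups and alternative model specifications. It does not say how large a deviation counts as substantial.

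Three other places bear on this. The WP2 section has a sensitivity analysis that does not depend on the trend check, but it is optional: "As sensitivity analyses, we may also further restrict the sample to a subset with relatively lower income and/or welfare dependency". The list of strengths and limitations after the abstract warns that "residual confounding may persist despite efforts to adjust for baseline differences". The later Strengths and limitations section admits that contextual factors could bias the analysis and adds: "The many IPS catchment areas and control areas help reduce the risk of contextual factors introducing unobserved confounding".

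**The concern.** Rollout was not randomised. The abstract describes local and national government projects. The section on IPS in Norway describes earmarked funding for six to eight pilot sites in 2012–2016, with responsibility passing to NAV from 2017. Areas that took up IPS early may have differed in where their employment or benefit rates were heading, as well as in their starting level.

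Complete coverage does not help with that, because it concerns who is in the data and not which areas adopted and when. DID removes differences that are constant over time, so what remains is differential trends and time-varying confounding. The protocol's safeguard against these is the pre-trend comparison, and the follow-up analyses start only when that comparison shows a problem. If it misses a real divergence, no analysis that the protocol commits to examines the divergence further.

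The stakes are highest for long-term effects, which the abstract emphasises. With data ending in 2019, a 2012 adopter contributes up to eight exposed years and a 2017 adopter three. The longest-run estimates therefore come from the sites with the shortest pre-period. The sample size section notes that only part of the target group was offered IPS even where it was available, so any population-level effect is diluted and more easily created or hidden by a modest trend difference. WP2 results also feed the economic model in WP3.

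**Working it through.** The protocol states no figure for this check, so there is none to reproduce. The sample size section gives no effect size and calls power calculations redundant. What follows is an illustration.

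**Inputs from the protocol article**
- Registry data 2009–2019 (WP2 section). A 2012 adopter has 3 pre-years (2009–2011); a 2017 adopter has 8 (2009–2016).
- Six to eight pilot sites (IPS in Norway section) and about 70 teams at the end of the window (WP2 section).

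**Assumptions, not in the documents**
- Seven pilot areas starting in 2012, compared with 63 others (about 70 areas in all).
- A linear differential trend δ of 0.3 percentage points a year.
- Independent area-year errors with SD s between 0.5 and 2.0 points.
- The check is a two-sided 5% test of the difference in pre-period slopes.

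As a rough guide to s, 82 500 people a year over 70 areas is 1,179 per area-year. For a dichotomous outcome, √(p(1−p)/1,179) is 1.17 points at p = 20% and 1.46 at p = 50%. The WP2 text derives 82 500 as 55% of 250 000, but 0.55 × 250 000 = 137 500. That gives 1,964 per area-year and 0.90 to 1.13 points. A proportion-of-time outcome has individual variance no larger than this, while area-level shocks add to it. A range of 0.5 to 2.0 covers both.

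**Formula**

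SE = s·√((1/g₁ + 1/g₀)/Sxx), where g₁ and g₀ are the numbers of areas and Sxx is the sum of squared centred pre-years. Power = Φ(δ/SE − 1.96) + Φ(−δ/SE − 1.96).

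**2012 pilots, 7 v 63, 3 pre-years.** Sxx = 1 + 0 + 1 = 2. At s = 1.0, SE = √((1/7 + 1/63)/2) = 0.282, δ/SE = 1.06 and power is 19%.

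**Power at δ = 0.3 points a year**

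| Cohort (assumed) | Sxx | s = 0.5 | s = 1.0 | s = 1.5 | s = 2.0 |
|---|---|---|---|---|---|
| 2012 pilots, 7 v 63, 3 pre-years | 2 | 57% | 19% | 11% | 8% |
| Later cohort, 20 v 30, 6 pre-years | 17.5 | >99% | 99% | 83% | 58% |
| 2017 cohort, 35 v 28, 8 pre-years | 42 | >99% | >99% | >99% | 97% |

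The pilot row depends little on the assumed comparison count. With an unlimited number of comparison areas, SE at s = 1.0 is √((1/7)/2) = 0.267 and power is 20%. With six or eight pilots out of 70 it is 17% or 20%.

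**What an undetected trend would do.** For a 2012 adopter the pre-period mean year is 2010 and the post-period mean year is 2015.5, a gap of 5.5 years. A trend of 0.3 points a year biases a simple pre/post DID by 0.3 × 5.5 = 1.65 points. At s = 1.0, the trend detectable with 80% power is (1.96 + 0.84) × 0.282 = 0.79 points a year, a bias of about 4.3 points.

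**Smaller trend.** At δ = 0.1 points a year (bias 0.1 × 5.5 = 0.55 points), power at s = 1.0 is about 6% for the pilots, 31% for the middle cohort and 72% for the 2017 cohort.

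**The case against.** The strongest reply is that the protocol claims less than a critic may read into it. Several stronger readings are tempting and should be set aside.

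- *The plan skips adjustment because the data are complete.* The sentence concerns matching for sample selection. The limitations list speaks of efforts to adjust for baseline differences, and nothing rules adjustment out. The covariates and estimator may be in an analysis plan that is not shown, so their absence is no finding.
- *Confounding is left uncorrected.* DID removes time-invariant area differences, and the protocol discloses residual and contextual confounding.
- *The pre-trend check has little power.* The documents do not show this. The figures rest on assumed area counts, SD and trend. In a staggered design later adopters have longer pre-periods, and at 0.3 points a year power there is adequate over most of the range.
- *The appeal to many areas is wrong.* The text says only that they help reduce the risk. Averaging over many areas does dampen local shocks, though it does not remove systematic selection into early adoption.
- *Pre-testing distorts the reported intervals.* Nothing makes the primary estimate or its publication depend on the check. A failed check only adds analyses, and the dissemination section commits to publishing nil findings.

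All of this stands. It does not answer the conditional rule itself. The one sensitivity analysis outside that rule is optional, and it restricts the sample by income, welfare dependency or education, which does not address differential area trends. Good power in later cohorts also gives little reassurance about the pilots, who supply the longest follow-up.

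**Conclusion.** The concern holds in a limited form. The protocol states a rule under which its trend-robustness analyses start only after an observed, undefined substantial deviation, and a quiet pre-trend comparison should not switch them off. The rationale from complete coverage supports less concern about sample selection and attrition; it does not bear on differential trends or time-varying confounding from non-random rollout.

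The weakness is plausible mainly for the six to eight early sites, where illustrative power is about 57% down to 8% as the assumed SD rises from 0.5 to 2.0 points. For cohorts with six to eight pre-years it is 58% or higher throughout, and above 80% except at the largest SD in the six-year case. These values assume a linear trend of 0.3 points a year and independent area-year errors; a smaller trend lowers power in every cohort.

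This is a cheap improvement to a sound design. It is not evidence that the results will be biased.

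**What to change.** In the text after Figure 1, replace the conditional sentence with a commitment that applies to both primary outcomes named under Ethics and dissemination (employment and welfare benefits), whatever the pre-trend comparison shows. Report:

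1. sensitivity bounds under limited violations of parallel trends, for example relative-magnitude bounds; and
2. a staggered DID estimate conditional on pre-exposure registry covariates, beside the unadjusted estimate.

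Which of the two estimates in item 2 is primary can be left to the analysis plan. A doubly robust estimator is one reasonable choice, but this point does not require it.

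Reword the rationale so that complete coverage is credited only with removing sample-selection and attrition problems. Make it consistent with the limitations list by saying where the efforts to adjust for baseline differences enter.

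The registry data are already held, so the cost is a little more analysis and wider reported uncertainty. The change should be made before the primary outcomes are analysed.
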